**Fig. 2 Fig2:**
[figure not shown]
Schedule of enrolment, interventions, and assessments

### Sample size {14}

Since phases 1 and 2 consist of a pilot study for the clinical evaluation of a biosensor prototype and the gamified application that considers a biofeedback system for performing physical exercises, a convenience sample of 15 individuals without medical contraindications for PA will be studied. Assuming a sample loss of 30%, we will recruit 20 participants.

The third phase will be a noninferiority, investigator-blinded randomized clinical trial of the individuals eligible for the study—considering the same eligibility criteria as in phases 1 and 2, in addition to being sedentary—will be divided into two groups: the intervention group (IG), which will receive the exercise protocol through the biosensor and gamified application, and the control group (CG), which will only receive guidelines for performing PA. Considering a confidence level of 95%, power of 80%, ratio of 1:1 between the CG and IG, and estimated prevalence of adherence to the protocol of 70% and 50% for the IG and CG, respectively, it would be necessary to allocate 104 individuals in each group. Adding 30% for possible follow-up losses, 149 sedentary individuals will be assigned to each group, totalling 298 subjects in the study.

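### For phases 1 and 2 the target of 15, the 30% loss and the 20 recruits do not agree: a 30% loss from 20 leaves 14

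*Protocol article*

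**What the plan says.** The Sample size {14} section of the protocol article has two paragraphs, and each applies a 30% loss allowance.

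- **Phases 1 and 2.** These are described as a pilot, in which "a convenience sample of 15 individuals without medical contraindications for PA will be studied". The next sentence reads: "Assuming a sample loss of 30%, we will recruit 20 participants". One loss rate is given for the two phases together.
- **Phase 3.** From an "estimated prevalence of adherence to the protocol of 70% and 50% for the IG and CG, respectively", the section concludes that "it would be necessary to allocate 104 individuals in each group". It then continues: "Adding 30% for possible follow-up losses, 149 sedentary individuals will be assigned to each group, totalling 298 subjects in the study".

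Neither paragraph states the formula that turns the target into the number recruited.

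**The concern.** A loss allowance exists so that the target number remains after the assumed loss. In phase 3 it does this. In phases 1 and 2, with the same percentage in the same section, it falls one short.

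The small sample supports the agreement analyses of the biosensor (paired comparisons, intraclass correlation, Bland–Altman), and agreement with the reference devices is listed first among the primary outcomes in Outcomes {12}. A reader should be able to tell from the section how many participants to expect at the end of the two phases. As printed, the text suggests 15 while its own loss rate implies 14.

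**Working it through.** **Inputs**, all from Sample size {14}: target 15, loss 30% and recruits 20 for phases 1 and 2; target 104 per group, allowance 30% and 149 per group (298 in total) for phase 3. The 104 is taken as given.

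**Step 1. Reproduce the printed recruitment figures.** Two formulas are in common use: multiply, n x (1 + d), or divide, n/(1 − d). With d = 0.30, rounding up:

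| | Target | Multiply | Divide | Printed |
|---|---|---|---|---|
| Phases 1 and 2 | 15 | 15 x 1.3 = 19.5, so 20 | 15/0.7 = 21.4, so 22 | 20 |
| Phase 3, per group | 104 | 104 x 1.3 = 135.2, so 136 | 104/0.7 = 148.6, so 149 | 149 |

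The printed 20 matches multiplication exactly; the printed 149 matches only division. Neither formula gives both.

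**Step 2. Apply the stated loss to the printed recruits.**

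- Phases 1 and 2: 20 x 0.70 = 14, one below 15.
- Phase 3: 149 x 0.70 = 104.3, so 104 is kept.
- Alternatives for phases 1 and 2: 21 x 0.70 = 14.7 and 22 x 0.70 = 15.4, so 22 is the smallest number whose expected remainder reaches 15.
- Twenty recruits leave 15 only if the loss is at most 1 − 15/20 = 25%.

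**Step 3. Size of the effect.**

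- *Precision.* Standard errors scale with 1/√n, so going from 15 to 14 multiplies interval widths by √(15/14) = 1.035, about 3.5%. Allowing also for the change in the t quantile makes it about 4.3%.
- *Chance of reaching 15.* Assume that each participant is lost independently with probability 0.30 over the two phases. Then P(Bin(20, 0.7) ≥ 15) = 0.416 and P(Bin(22, 0.7) ≥ 15) = 0.671.
- *Dependence on when losses occur.* The protocol does not split the 30% between the phases. If the loss by the end of phase 1 were 10% or 20% (assumed values), the chance of at least 15 from 20 at that point would be about 99% or 80%.

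**The case against.** Four points can be made for the plan.

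1. **The size is trivial and nothing depends on 15.** This stands. The 15 is a convenience number without a power or precision calculation, and none of the progression criteria in Statistical methods {20a} names a required number of participants. It limits the consequence but does not make the three figures agree.

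2. **The protocol states no formula, so multiplication is inferred.** This stands too. Twenty might be a round number chosen near 21.4. All that can be said is that 20 is consistent with multiplying. That 30% of 20 leaves 14 needs no such inference.

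3. **The 30% might be meant as an add-on rather than a loss.** This does not help. The add-on wording appears in phase 3 ("Adding 30% for possible follow-up losses, 149 sedentary individuals will be assigned to each group"), where the number comes from division. The phase 1 and 2 sentence speaks of a loss. No single meaning of 30% gives both 20 and 149.

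4. **The biosensor validation that gates progress is not shown to be at risk.** A reader might infer from the 42% that this validation will more likely than not end below its stated size. The document does not support that. The numerical gate, agreement within 5%, belongs to phase 1, which consists of two walk tests at most a week apart. The six-week training belongs to phase 2, whose gate is whether the application works. The 30% covers both phases together, so the 42% applies only to completing both.

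**Conclusion.** The point holds as a small internal inconsistency. With 20 recruits and the stated 30% loss, the expected number completing phases 1 and 2 is 14, not 15, whereas the phase 3 allowance is correctly sized.

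That conclusion rests only on printed figures and on reading the 15 as the number meant to remain after losses. This is the natural reading, although the text does not label it so. The 42% further assumes independent losses at the full 30% across both phases.

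The shortfall is one participant, with intervals about 3.5% wider. No decision rule or conclusion of the trial turns on it, and the phase 3 numbers (149 per group, 298 in total) stand.

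**What to change.** Amend the sentence in Sample size {14} to say that 20 participants are recruited and that, with a 30% loss, about 14 are expected to complete phases 1 and 2. The cost is one sentence and an expected number lower by one. No analysis changes.

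Recruitment for the exploratory study began in August 2022 (Trial status), so correcting the statement is more practical than changing the recruitment number. Had the phase 3 calculation been used from the start, the figure would have been 22.

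Lowering the stated loss to 25%, so that 20 recruits leave 15, is not advisable. It would fit the assumption to the recruitment figure without evidence and leave two unexplained loss rates in one section.

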### Recruitment {15}

The recruitment of sedentary individuals will involve a cross-sectional investigation that will utilize the International Physical Activity Questionnaire (IPAQ), which assesses the frequency, duration, and type of physical activity an individual engages in across various settings, such as work, transportation, leisure time, and domestic chores. This outreach endeavour will be geared towards the broader population, focusing on identifying potential eligible candidates for the study within a specific city in southern Brazil. To achieve random allocation between the CG and the IG, a preliminary cross-sectional study targeting the general population will be executed. This study aims to pinpoint sedentary individuals suitable for inclusion in the randomized clinical trial.

Consequently, considering a confidence level of 95%, a power of 80%, an estimated sedentary lifestyle prevalence of 50%, and a margin of error of 2 percentage points, it will be imperative to interview 2875 individuals (factoring in a 20% allowance for possible losses and refusals). This approach is designed to successfully identify an adequate number of sedentary individuals for participation in the randomized trial’s phase 3.

## Assignment of interventions: allocation

### Sequence generation {16a}

We will employ a computerized random number generator to allocate individuals to either the IG or the CG in a 1:1 ratio. Given the potential variability in VO2 values based on age and gender, we have chosen to utilize block randomization. This method will help us ensure that there is a comparable distribution of age and gender between the two groups, thereby mitigating any potential bias.

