### Eligibility criteria {10}

The recruitment of individuals will adhere to specific inclusion criteria: (i) individuals aged between 20 and 60 years without medical contraindication to engage in physical exercise, (ii) possession of a smartphone (cell phone with Android operating system), and (iii) willingness to participate in the research by signing the informed consent form. The exclusion criteria were experience angina during exertion, history of acute myocardial infarction within the 12 months prior to the start of the protocol, require oxygen supplementation, exhibit clinical instability in the month preceding the protocol initiation, uncontrolled hypertension, visual diseases that prevent the performance of the protocol, chronic conditions hindering participation in the exercise protocol, illiterate, and refuse to sign informed consent form.

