### Outcomes {12}

Primary outcomes will encompass the following: (1) the concordance between HR and step count measurements assessed by the biosensor under test compared to standard devices (Polar H10 and ActiGraph, respectively); (2) participant perception regarding the utility of the gamified application for exercise engagement; (3) comparison with the prevalence of adherence to the physical activity protocol between the control and intervention groups; (4) evaluation of exercise capacity through ISWT, including stage and the corresponding phase at which the test was halted; and (5) measurement of oxygen consumption (VO_2_).

Secondary outcomes will include the following: (1) tissue oxygenation assessed via near-infrared spectroscopy (NIRS), (2) subjective perception of exertion during ISWT, (3) evaluation of endothelial function, and (4) assessment of autonomic function.

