For phase 3, a qualitative analysis will be performed on participants’ diary reports and a quantitative assessment of potential gamified application failures. Step count measured by the biosensor will be compared to the ActiGraph accelerometer using Student’s *t*-test or Wilcoxon rank-sum test, depending on residual distribution. Agreement between step counts will be evaluated using Bland–Altman test, Lin’s correlation coefficient, and intraclass correlation coefficient. Pre- and post-exercise protocol data, encompassing functional capacity, VO_2_, tissue oxygenation, maximum and resting HR, systemic blood pressure, subjective exertion perception, endothelial function, and HRV, will be analysed using Student’s *t*-test for paired samples or Wilcoxon signed-rank test, aligned with residual distribution. Participants achieving a minimum of 70% completion of the prescribed protocol will be classified as adherent. As the random allocation is anticipated to ensure baseline comparability between the control and intervention groups, unadjusted analyses will primarily be carried out. In the event of any non-comparability in baseline characteristics due to chance, appropriate adjustments will be made to prevent potential biases. Significance level will be set at *p* < 0.05. The data will be analysed using Statistical Package for the Social Sciences (SPSS) 20.0 (SPSS, Chicago, IL, USA).

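### Block randomisation is credited with balancing age and gender, but without stated strata it balances only arm sizes, and adjustment is left until imbalance is seen

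*Protocol article*

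**What the plan says.** Under Sequence generation {16a}, a computerised generator will "allocate individuals to either the IG or the CG in a 1:1 ratio". The reason for the method follows: "Given the potential variability in VO2 values based on age and gender, we have chosen to utilize block randomization". The result expected from it is: "This method will help us ensure that there is a comparable distribution of age and gender between the two groups". Neither that section nor Concealment mechanism {16b} or Implementation {16c} mentions strata, minimisation or separate lists by age or gender.

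Under Statistical methods for primary and secondary outcomes {20a}, the phase 3 text says that "unadjusted analyses will primarily be carried out", and then: "In the event of any non-comparability in baseline characteristics due to chance, appropriate adjustments will be made to prevent potential biases". It names neither the covariates nor what would count as non-comparability.

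Outcomes {12} lists VO2 and walk-test exercise capacity among the primary outcomes. Eligibility criteria {10} admits "individuals aged between 20 and 60 years without medical contraindication to engage in physical exercise", so the age spread is wide.

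**The concern.** The design section attributes to blocking a property that blocking does not have. Permuted blocks on a single list force the arms to stay close in number as recruitment proceeds. They carry no information about who is in each block, so they leave age and gender to chance. Balance beyond chance needs blocks run within age and gender strata, or minimisation on those factors.

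The analysis section does not make up for this. Having named age and gender as prognostic for VO2, the plan leaves them out of the primary analysis and brings covariates in only if the observed groups look different. That discards precision known in advance to be available. It also leaves the choice of covariates, and the decision to adjust at all, until the data have been seen.

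**Working it through.** **The plan's sample size.** Sample size {14} gives 95% confidence, 80% power, a 1:1 ratio and adherence of 70% versus 50%. The two-sided, two-proportion formula with pooled variance is

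n = [1.960·√(2·0.6·0.4) + 0.842·√(0.21 + 0.25)]² / 0.20² = 93.0.

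With continuity correction: (93.0/4)·[1 + √(1 + 4/(93.0·0.20))]² = 102.8, so 103, against the stated 104. Allowing for losses: 104/(1 − 0.30) = 148.6, so 149 per group and 298 in total, as stated. The sample size reproduces to within one participant and is not in dispute. It serves here only to size chance imbalance.

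**Assumptions not in the protocol.** 50% women (70% also tried); age uniform over 20 to 60; block sizes of 4 and 6; age strata cut at 40 years.

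**Chance imbalance by formula, no stratification.**
- Sex: SD of the difference in proportion of women = √(2·0.25/149) = 0.058. The normal approximation gives P(difference > 0.10) = 0.084. Allowing for whole counts (at least 15 women more in one arm, so a cut at 14.5/149 = 0.097) gives 0.093.
- Age: SD of a uniform age = 40/√12 = 11.55 years. SD of the difference in means = 11.55·√(2/149) = 1.34 years. P(difference > 2 years) = 0.135.

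**Simulation at 298 participants, 5,000 trials per scheme, 50% women.**

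| Scheme | SD of arm-size difference | SD of sex difference (points) | P(sex > 10 points) | SD of mean-age difference (years) | P(age > 2 years) |
|---|---|---|---|---|---|
| Simple randomisation | 17.4 | 5.75 | 8.2% | 1.35 | 13.6% |
| Blocks of 4, one list | 1.2 | 5.81 | 9.2% | 1.34 | 13.1% |
| Blocks of 6, one list | 1.3 | 5.82 | 9.6% | 1.35 | 14.0% |
| Blocks of 4 in sex-by-age strata | 1.8 | 0.62 | 0.0% | 0.68 | 0.3% |

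Blocking changes the arm-size column and nothing else. The small differences between simple and blocked schemes for sex and age are simulation noise and rounding to whole counts. With 70% women the picture is the same: P(sex > 10 points) is 5.9% for simple randomisation, 6.6% to 6.7% for unstratified blocks and 0.0% for stratified blocks, and P(age > 2 years) is 0.4% with stratified blocks.

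**After 30% random loss.** About 104 per arm remain (149·0.70).
- Unstratified: SD = √(2·0.25/104) = 0.069, so P(> 0.10) = 0.149 and P(> 0.05) = 0.47.
- Stratified: the sex mix is fixed at entry and only the loss is random, so SD ≈ √(2·0.25·0.30/104) = 0.038, P(> 0.10) = 0.008 and P(> 0.05) = 0.19.

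Simulation of 4,000 trials agrees: above 10 points in about 15% versus about 1%, and above 5 points in 46% to 48% versus about 20%.

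**Adjusting only when imbalance is found.** Simulated type I error with no true effect, one covariate explaining a share R² of the outcome, 10,000 trials per row, and adjustment triggered by p < 0.05 on a baseline test. That trigger is assumed, because the plan states none.

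| R² | Unadjusted | Always adjusted | Adjusted only after a significant baseline test |
|---|---|---|---|
| 0.2 | 5.2% | 5.5% | 4.7% |
| 0.4 | 5.0% | 5.0% | 3.9% |
| 0.6 | 4.7% | 4.9% | 3.0% |

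The conditional rule falls below the nominal 5%. Unconditional adjustment stays at about 5% and removes roughly the share R² from the residual variance.

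**The case against.** **Blocks may mean strata.** In experimental-design usage, blocks formed on age and gender are strata, and a condensed article may leave cut-points and block sizes to the full protocol. That reading is possible. But the text names no strata and credits the balance to blocking itself, so it needs correcting even if stratified blocks were intended.

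**Randomisation is unbiased anyway.** This stands. A reader might infer that allocation, or the treatment comparison, is biased. The documents do not support that: age and gender are balanced in expectation under any of these schemes, and about 90% of unstratified trials stay within 10 points on sex.

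**An unadjusted primary analysis is valid, and covariate lists belong in an analysis plan.** Validity stands, as the unadjusted column shows. The point is not that a list is missing. The protocol commits to a data-dependent rule while naming prognostic factors that it then leaves out. A reader might also infer that the rule inflates false positives. With one covariate and a fixed trigger it was conservative. Free choice among several covariates was not simulated, so inflation from that route is possible but not shown.

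**The effect on outcomes is limited.** Much of this stands. The sample size rests on adherence, for which the protocol claims no relation to age or gender. The phase 3 text describes paired pre/post tests for VO2 and functional capacity, in which stable differences in level largely cancel. The imbalance figures were not carried through to VO2 or walk-test results.

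**Stratification does not guarantee near-perfect balance.** This stands for outcomes measured at six weeks. The near-zero figures hold at randomisation only. With 30% random loss, about 20% of stratified trials still differ by more than 5 points on sex among completers.

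**Conclusion.** The point holds in a limited form. The sequence-generation section claims balance on age and gender from a method that, as described, controls arm sizes only. With 298 participants, chance leaves a sex difference above 10 points in about 9% of trials and a mean-age difference above 2 years in about 13%. Stratified blocks reduce both to 0.4% or less at randomisation. Among completers after 30% random loss, they reduce a sex difference above 10 points from about 15% to about 1%. These figures rest on the assumed sex mix, age distribution, block sizes and age cut. That unstratified blocks add no balance on age or gender does not depend on them.

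The consequence is chance imbalance and lost precision on VO2 and walk-test capacity, with room for discretion in the adjusted model. It is not biased allocation, and a raised false-positive rate has not been shown. The correction should be made, but nothing here invalidates the trial.

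**What to change.** 1. **Sequence generation {16a}:** state permuted blocks stratified by sex and age band (for example 20 to 39 and 40 to 60 years), and attribute the balance to the stratification. If strata are already in use, say so.
2. **Statistical methods {20a}, phase 3:** replace the conditional rule with wording such as: between-arm comparisons of phase 3 outcomes are adjusted for sex, age and, for continuous outcomes, the baseline value, whatever the observed balance; unadjusted results are given as a sensitivity analysis.
3. **Scope:** leave the biosensor-versus-ActiGraph agreement analyses and the within-person paired tests unchanged, since covariate adjustment between arms has no place there. Binary adherence is adjusted for sex and age only.
4. **Baseline value:** Participant timeline {13} puts the initial assessment after randomisation, and participants are not blinded. State whether participants know their group at that visit, because the baseline walk test and VO2 are to serve as covariates.

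The cost is four envelope sets in place of one and slightly more analysis work; the sample size does not change. Trial status schedules recruitment to the randomised trial from June 2023. If allocation has already begun on a single list, the analysis change still applies and recovers most of what can be recovered.

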### Concealment mechanism {16b}

The allocation sequence for this process will be implemented using sealed envelopes to maintain the integrity of the randomization process.

### Implementation {16c}

Notably, the researcher entrusted with generating the allocation sequence will remain uninvolved in participants’ data collection. Additionally, the investigator responsible for conducting the functional assessments will be kept blind to the participants’ allocation status.

## Assignment of interventions: blinding

### Who will be blinded {17a}

Owing to the nature of our intervention, which encompasses physical activity and gamification, participant blinding will not be feasible. However, the researcher overseeing the evaluation process will be kept blinded.

### Procedure for unblinding if needed {17b}

Unblinding will not be permitted at any point during the study due to its inherent design and the nature of the interventions involved.

## Data collection and management

### Plans for assessment and collection of outcomes {18a}

Participants will be provided transportation vouchers for their visits to Universidade Federal de Ciências da Saúde de Porto Alegre. Reminder calls will be placed to inform participants of their assessment days. During the intervention, no proactive contacts will be initiated to enhance adherence, as adherence is one of the evaluated outcomes.

### Plans to promote participant retention and complete follow-up {18b}

Since one of the study’s goals is to assess the impact of gamification on adherence to PA, no specific measures will be undertaken during the study to bolster adherence. Upon the study’s conclusion, all participants will be contacted for a final assessment. For measuring adherence, the intervention group will register their adherence via a dedicated application. Meanwhile, the control group will be guided to record their physical activities on a weekly basis added to plans to promote participant retention and complete follow-up.

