### Phase 3: Evaluation of gamified in uncontrolled environment

Phase 3 comprises a noninferiority, investigator-blinded, randomized clinical trial with two distinct groups: the intervention and control groups. Participants within the intervention group (IG) will install the gamified application on their smartphones and use a biosensor during exercise sessions. These sessions will align with the prescribed intensity derived from the ISWT, following the 6-week regimen detailed in phase 2. Participants will be duly instructed to cease exercising if they experience symptoms like chest pain, discomfort, or dizziness.

Within the gamified application, participants will have access to a diary feature, enabling them to log notifications received and their efforts during exercise, both monitored by the biosensor and the gamified app. On the other hand, individuals in the control group (CG) will receive instructions to engage in physical activity at home without biosensor monitoring. They will use the app independently, aiming for a minimum of 300 min per week at moderate intensity or at least 150 min per week at vigorous intensity (self-assessed).

Preceding and following the 6-week period, both the IG and CG will undergo assessments akin to those conducted in phase 1. These include evaluations of functional capacity, muscle oxygenation, and further assessments led by trained and blinded researchers.

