### Strategies to improve adherence to interventions {11c}

Following participant randomization, the research team will refrain from implementing specific operational measures to ensure the desired follow-up level. This approach aligns with one of the study’s primary objectives, which is to assess exercise adherence facilitated by gamification. What will be done is to send a standard message weekly to both groups requesting weekly recording of the activity carried out during the week in a spreadsheet.

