### Gamification’s role in promoting PA

Gamification interventions have shown potential in boosting PA participation and self-monitoring while also promoting a sense of enjoyment. However, the literature lacks exploration of the impact of combining gamification with wearable activity devices for promoting PA, as evidenced by divergent findings from a recent systematic review [16]. This study aims to address this gap by investigating the effects of this combination. The hypothesis is that merging gamification with wearable devices can lead to improved adherence to exercise routines.

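### Two sections give the effect of gamification on adherence as an objective, but phase 3 randomises a whole package against activity guidelines and cannot attribute a difference to gamification.

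*Protocol article*

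**What the plan says.** Two operational sections state the goal as gamification itself. Section {11c} justifies having no adherence support after randomisation by reference to "one of the study’s primary objectives, which is to assess exercise adherence facilitated by gamification". Section {18b} gives the same reason, that one of the study's "goals is to assess the impact of gamification on adherence to PA".

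The intervention is wider than that. In the phase 3 description, intervention participants "will install the gamified application on their smartphones and use a biosensor during exercise sessions". The same section continues: "These sessions will align with the prescribed intensity derived from the ISWT, following the 6-week regimen detailed in phase 2". The phase 2 text on exercise prescription adds that the app displays intensity and heart rate, and it lays out the sessions (warm-up, step training, cool-down, with a shorter interval format in week 1). Sample size {14} describes the intervention group as the one "which will receive the exercise protocol through the biosensor and gamified application", and sets 70% adherence there against 50% in controls.

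The abstract and Sample size {14} give controls guidelines only. The phase 3 description has them exercise at home without the sensor, judge intensity themselves and aim for the same weekly minutes. It also says that they use the app on their own.

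The Discussion states the aim differently. After describing the lack of work on gamification combined with wearable devices, it says: "This study aims to address this gap by investigating the effects of this combination".

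**The concern.** A two-arm trial estimates one contrast: everything that differs between the arms, taken together. Here the game is not the only thing that differs. Intervention participants also see their heart rate through a sensor, have an intensity set from their own test, and follow laid-out sessions. Any of these could change the proportion who complete 70% of the prescribed protocol, which is the adherence criterion.

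If sections {11c} and {18b} are taken at their word, a positive result would be read as showing that gamification raises adherence. Someone using the result could then adopt a game without the sensor or the individual prescription, which this trial does not test. Comparison of adherence between the arms is listed among the primary outcomes, so the wording of its objective governs a main conclusion of the trial.

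**Working it through.** **1. The plan's own figure.** Inputs from Sample size {14}: 70% v 50%, 95% confidence (taken as two-sided 5%), 80% power, 1:1 allocation, 30% losses.

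- Uncorrected: n = [1.960·√(2·0.6·0.4) + 0.842·√(0.7·0.3 + 0.5·0.5)]² / 0.2² = (1.358 + 0.571)² / 0.04 ≈ 93 per arm.
- With continuity correction: n' = (n/4)·[1 + √(1 + 4/(n·0.2))]² = (93/4)·(1 + 1.102)² ≈ 103 per arm, against 104 stated.
- Losses: 104 / 0.70 = 148.6, rounded up to 149 per arm; 2 × 149 = 298, as stated.

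The figures hold up. Both percentages are given for the intervention and control groups as defined in that paragraph, so the sizing is for the package contrast.

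**2. The arms side by side.**

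| Feature | Intervention | Control | Differs? |
|---|---|---|---|
| Gamified app | Yes | No (abstract, {14}); used independently (phase 3 description) | Unsettled |
| Biosensor with heart-rate feedback | Yes | No | Yes |
| Intensity | Derived from own walk test | Self-assessed | Yes |
| Session structure | 6-week step regimen from phase 2 | None described | Yes |
| Weekly volume target | 300 min moderate or 150 min vigorous | Same | No |

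**3. What the contrast identifies.** Write G for the game, S for the sensor with its heart-rate feedback (one delivery chain, counted once), and R for the individual prescription with its session structure. On the guidelines-only reading, G, S and R are all present in one arm and all absent in the other. They are perfectly aligned with allocation, so the difference in adherence is the joint effect of G, S and R, including any interactions. No covariate or model separates them, because no participant is randomised to S and R without G.

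If controls do use the gamified app, G is present to some degree in both arms. The contrast then rests more on S and R, and attribution to gamification is weaker still.

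**4. The Discussion's version of the aim.** Gamification plus wearables covers G and S. R also differs and is not named. The Discussion is closer to the design than {11c} and {18b}, but it still describes less than what is randomised.

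**The case against.** The strongest reply is that the defining sections already describe a package. Objectives {7} speaks of a biosensor and an app. Trial design {8} describes an application that incorporates biofeedback. Outcomes {12} compares adherence between groups without mentioning gamification, and the Discussion's hypothesis concerns gamification merged with wearables. On this view, {11c} and {18b} are side remarks explaining why no reminders are sent, with gamification used as shorthand. Testing a multicomponent package is also a legitimate design.

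Much of this stands. The design needs no defence, and no extra arm is called for. But {11c} does call the gamification aim a primary objective, and the shorthand is not explained. The Discussion's combination also omits the individual prescription.

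Three stronger readings are tempting and are not supported:

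- A reader might infer that the Discussion promises proof that gamification works. It does note that the literature on gamification's efficacy is insufficient. However, the evidence it promises is for public health decisions on exercise, and its closing paragraph refers to gamification combined with wearable devices.
- A reader might count sensor, feedback, prescription and regimen as separate non-game components. Sensor and feedback are one chain, the weekly volume target is equal, and the Discussion lists feedback and goal-setting among its gamification elements. The individual prescription with its session structure, and the sensor hardware, clearly remain. The prescription alone is enough to block attribution.
- A reader might infer that the trial is underpowered for gamification. No gamification-only test is planned and the documents give no share of the 20 points for it. A power figure would describe an analysis that does not exist.

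**Conclusion.** The concern holds as a mismatch between a stated objective and the randomised contrast. Phase 3 can answer whether the whole package changes adherence compared with guidelines. It cannot answer the question as worded in {11c} and {18b}.

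The severity is minor: no stated number is wrong, the arms are usable as they are, and other sections already frame the question more nearly correctly. The size of any misattribution cannot be given, because the documents offer no basis for splitting the assumed 20-point difference (70% − 50%). It should not be bounded at 0 to 20 points either, since a component could reduce adherence or interact with another.

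The conclusion does not depend on how the control arm's app use is resolved. Under guidelines only, the game is inseparable from the other components. Under app use by controls, the contrast in gamification shrinks or disappears.

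**What to change.** - In {11c} and {18b}, name the whole package versus activity guidelines as the object of the adherence comparison: gamified app, biosensor with heart-rate feedback, and walk-test-based prescription within the structured 6-week regimen.
- In the Discussion, under the role of gamification in promoting activity and its evolving role in health care, extend the aim and intended conclusion to that package, including the individual prescription.
- State that phase 3 does not estimate the separate effect of gamification, and in Sample size {14} that 70% v 50% refers to the package.
- Reconcile the phase 3 description, which has controls using the app, with the abstract and Sample size {14}, which give them guidelines only. The comparator wording above should follow whichever is intended.

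These are wording changes. They need no change to sample size or visits and no additional arm. The cost is a narrower claim: the trial could not be cited as evidence for gamification alone.
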